Exploration of the barriers and facilitators to abstinence and understanding what elements affect the psychiatric symptomatology and the main drug use are relevant to patients in SUD treatment. Acquiring such information will allow the scientific community to design personalized approaches to promote cessation [27, 28] within this vulnerable group. Previous studies associated smoking cessation in this population with sociodemographic variables (i.e., low education level, low socioeconomic status) [29] and other components, such as motivation to quit smoking, self-efficacy, previous experience with quitting smoking [30], expected withdrawal symptoms [31], and assessment of the services received [9]. Proactively identifying positive predictors of change among smokers in this population may help promote smoking cessation; the most frequently reported predictors are a high level of motivation, having had previous quit attempts, and reducing the number of CPD [13, 14].

Barriers to addressing tobacco use during addiction treatment have also been identified among clinicians. The main barriers are lack of knowledge and training, the preconception that quitting smoking simultaneously while being treated for use of other drugs may compromise abstinence, and clinicians’ smoking status [20].

The high number of SUD treatment admissions for alcohol and/or cannabis use, the high prevalence of tobacco use, and the limited number of interventions aimed at promoting smoking cessation in this group prompts research to facilitate new and better interventions in these settings. We designed the ACT-ATAC (“*Abandono del Consumo de Tabaco durante la Atención y el Tratamiento para Alcohol y/o Cánnabis*” [Tobacco cessation among smokers under alcohol and/or cannabis treatment]) study, which aims to:

(1) Explore clinicians' perceptions of the barriers and facilitators (individual and contextual) that influence the implementation of smoking cessation interventions, and the appropriateness of simultaneous or sequential interventions aimed at this group.

(2) Describe changes in tobacco use, motivation to quit, and the barriers/facilitators to quit at the start of treatment and after 12 months of follow-up.

(3) Identify the individual and contextual predictors associated with successful smoking cessation among persons treated for alcohol and/or cannabis use disorder in SUD programs in Barcelona.

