#### Variables

Dependent variables include tobacco use, cannabis use, and alcohol use. Tobacco use is rated yes/no. If answering “yes”, we ask the about the tobacco consumption pattern, including nicotine dependence using the 6-item Fagerstrom test [35], and the type of tobacco or other products consumed (i.e., cigarettes, roll-your-own tobacco, combination of both, cigars, e-cigarettes, iQOS); smoking history, including the age when the participant starting smoking, maximum abstinence time, previous quit attempts, and resources used (i.e., none, self-help, professional support, pharmacological treatment, etc.); motivation to quit smoking, measured by a Likert scale from 0 to 10; and willingness to quit smoking, assessed by a 4-item questionnaire that, according to Prochaska and DiClemente’s model, classifies smokers into five stages: pre-contemplative, contemplative, preparation, action, and maintenance [36].

Cannabis use is rated yes/no. If “yes”, we recorded users pattern of consumption, problematic use (yes/no) [37], withdrawal symptoms identified using the Marijuana Craving Questionnaire [38] and reasons for use [39]. Alcohol use is rated yes/no and described according to the variables of consumption included in the Alcohol Use Disorders Identification Test (AUDIT) [40, 41]. A fourth dependent variable is participants’ self-reported smoking knowledge, attitude, and services (S-KAS) received during their treatment in SUD programs [42].

The primary outcome is abstinence from smoking (yes/no), which is self-reported and verified by the exhaled CO concentration only if they report to be abstinent. Self-reported abstinence is defined as “no smoking in the 7 days prior to the assessment point.” Seven-day abstinence was chosen as the consumption measure based on the consensus recommendation in practice guidelines for the assessment of abstinence in patients who are not motivated to quit smoking and who may remain abstinent during various periods of the study [43]. Number of quit attempts in the last year of  > 24-h duration [44] were also recorded. All dependent variables are assessed at baseline and 3, 6, and 12 months of follow-up (Table 1).

**Table 1 Tab1:** Study variables and collection time points (at baseline and follow-up)

Variables	Follow-up							
	Baseline	1 week	3 months		6 months		12 months	
			Abstinent	Not abstinent	Abstinent	Not abstinent	Abstinent	Not abstinent

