**Tobacco**								
Type of tobacco or other products consumed and quantity	X			X		X		X
Nicotine dependence	X			X		X		X
Age at first consumption	X							
Age at start of regular consumption	X							
Previous attempts to stop smoking in their entire consumption trajectory	X							
Previous attempts to quit smoking in the last year	X							
Previous attempts to quit smoking since the last questionnaire				X		X		X
Maximum withdrawal time	X							
Resources used to quit smoking	X		X	X	X	X	X	X
Motivation to quit smoking	X			X		X		X
Smoking cessation provision	X		X	X	X	X	X	X
Efficacy	X		X	X	X	X	X	X
Level of smoking approach received	X	X	X	X	X	X	X	X
Environment	X							
Abstinence from consumption	X		X	X	X	X	X	X

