## Statistical analysis

After finishing the recruitment and follow-up, abstinence and quit attempt incidence rates will be calculated at baseline and at 3, 6, and 12 months according to whether participants have received any type of smoking cessation intervention. We will also calculate the corresponding risk ratios with 95% confidence intervals (CIs) for quitting and quit attempts.

We will assess the association between receiving smoking cessation support and the two primary outcomes (abstinence and quit attempts) using a Poisson regression model with robust variance for several independent variables (the substance of treatment, sex, types of cessation support [e.g., tobacco-related counselling and medication, etc.]), resulting in RRs with their 95% CIs as their estimators. For analysis, we will use SPSS for Windows version 21 with significance set at p  < 0.05.

We will also conduct exploratory factor analysis for testing the psychometric properties of the S-KAS and S-KAP scales.

S3 (months 40–44): Phenomenological study with discussion groups directed towards patients (will be conducted between December 2022 and June 2023).

This qualitative phenomenological study with discussion groups will use a semi-structured script to answer aim 4.

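### The stated model for cessation support adjusts only for treated substance and sex, and leaves out baseline motivation, previous quit attempts and nicotine dependence, so the RR for support can be confounded

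*Protocol article*

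**What the plan says.** The Statistical analysis section gives the main comparison: "We will assess the association between receiving smoking cessation support and the two primary outcomes (abstinence and quit attempts". The method is Poisson regression with robust variance, "for several independent variables (the substance of treatment, sex, types of cessation support". The e.g. in that sentence sits inside the bracket on support types and does not open the covariate list itself. The same section splits incidence rates at baseline, 3, 6 and 12 months "according to whether participants have received any type of smoking cessation intervention". It states no rule that support must come before the outcome.

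The Background says of cessation in this population that "the most frequently reported predictors are a high level of motivation, having had previous quit attempts, and reducing the number of CPD". Aim 3 is to "Identify the individual and contextual predictors associated with successful smoking cessation among persons treated for alcohol and/or cannabis use disorder".

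The Tobacco block of Table 1 marks motivation, nicotine dependence and quit attempts in the last year for collection at baseline. It records "Smoking cessation provision" at baseline, 3, 6 and 12 months, and "Level of smoking approach received" at those visits and at 1 week. On the outcome side, the Variables section says: "All dependent variables are assessed at baseline and 3, 6, and 12 months of follow-up".

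**The concern.** Support is not randomised here. A patient who wants to quit is more likely to seek or accept help and also more likely to quit. The Background supplies the link from motivation to the outcome. It also suggests a link to the exposure, since it ties some clinicians' reluctance to intervene partly to patients' low motivation. A model that holds only substance and sex constant leaves this path open, and the Limitations section does not mention it.

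Timing is a second, lesser problem. Support and abstinence are recorded at the same visits, and abstinence covers only the preceding 7 days. Support obtained because someone had decided to quit, or after they had quit, can therefore count as exposure. For quit attempts the overlap is closer still, because resources used to quit are used within an attempt.

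At stake is the RR for support, which the Discussion expects to inform future programmes in the Spanish healthcare system.

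**Working it through.** The plan states no figure on this point, so there is none to reproduce. The documents give no motivation shares, no strength of the link between motivation and quitting, and no support rates. Every input below is an assumption unless marked otherwise.

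**1. Confounding by motivation, with no true effect of support.** Let *a* and *b* be the shares of motivated patients among the supported and the unsupported, and RRm the risk ratio of quitting for motivated against other patients. Then

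apparent RR = (a·RRm + 1 − a) / (b·RRm + 1 − b).

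| RRm | 50% v 30% | 60% v 30% | 70% v 30% | 80% v 20% |
|---|---|---|---|---|
| 1.5 | 1.09 | 1.13 | 1.17 | 1.27 |
| 2 | 1.15 | 1.23 | 1.31 | 1.50 |
| 3 | 1.25 | 1.38 | 1.50 | 1.86 |
| 4 | 1.32 | 1.47 | 1.63 | 2.12 |

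A middle case is RRm = 3 with 60% v 30%: (1.8 + 0.4)/(0.9 + 0.7) = 2.2/1.6 = 1.38. Conditioning on motivation returns 1.00, but only by construction of the example.

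**2. The opposite direction.** Apply the same formula to dependence, assuming that highly dependent smokers quit half as often (RR 0.5) and are over-represented among the supported:
- 50% v 30%: 0.75/0.85 = 0.88
- 60% v 30%: 0.70/0.85 = 0.82
- 80% v 20%: 0.60/0.90 = 0.67

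The net bias therefore has no guaranteed sign.

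**3. Yardstick.** The sample-size paragraph (Sampling method) gives 7 and 10 ex-smokers per 100 patient-years, a ratio of 10/7 = 1.43, although it calls this 2.0; that mismatch is a separate matter. The paragraph contrasts contact with care against unassisted quitting, not supported against unsupported patients, so it gives only a sense of scale. On that scale, the middle case is nearly as large as the effect the study hopes to see.

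**4. False positives in favour of support.** Assume a spurious RR of 1.38, equal groups, 10% quitting overall and the protocol's 20% losses. The chance of a significant result favouring support is then 9.9% at 200 recruited and 11.3% at 250, against a nominal 2.5%.

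**5. Timing, with no true effect.** Assume that 50% are supported regardless of outcome, 10% quit, and a fraction *q* of unsupported quitters obtain support after quitting but before the visit. With q = 0.2:
- Supported quitters: 0.1 × (0.5 + 0.5 × 0.2) = 0.06, out of 0.51 supported.
- Unsupported quitters: 0.1 × 0.5 × 0.8 = 0.04, out of 0.49 unsupported.
- RR = (0.06/0.51)/(0.04/0.49) = 1.44.

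Over q = 0.05 to 0.30 the RR runs from 1.09 to 1.75.

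**6. Room for adjustment.** At 10% quitting and 20% losses, expected abstinent participants number 200 × 0.8 × 0.10 = 16 to 250 × 0.8 × 0.10 = 20. Motivation, attempts, Fagerström score and sex (one parameter each), substance in three classes (two) and support (one) make seven parameters. That is 16/7 = 2.3 to 20/7 = 2.9 events per parameter, so the covariates need to be few or condensed.

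**The case against.** The article is a condensed account of an observational study, and it speaks of an association. A fuller covariate list and an exposure window could stand in an analysis plan that is not shown. That would answer a complaint about silence. It does not answer this one, because the article gives a list, and the list omits predictors that its own Background puts first.

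The objection does rule out several stronger readings:

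- *That the plan lays down a rule counting support up to the outcome visit.* This is an inference from the wording on receipt read with Table 1. The text gives no window, and support recorded earlier is available.
- *That the bias can only inflate the RR.* Support includes clinician-initiated advice and medication. If these are directed to more dependent smokers, the bias can run below 1.
- *That baseline cigarettes per day is a named predictor left out.* The Background names reducing consumption, which is a change over time.
- *That patients who stay longer have more time to become supported.* Abstinence is a 7-day measure at fixed visits, and everyone assessed at a given visit has had the same time.
- *That aim 3 goes unanswered.* The bracketed list may not be the whole analysis, since the Variables section describes many more variables.
- *That taking support at 1 week as the only exposure would cure the problem.* Motivated patients may also receive more early support, and all later support would be classed as none.

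**Conclusion.** The concern holds for the covariate list. As written, the RR for support is adjusted only for substance and sex, and it is open to confounding by motivation, previous attempts and dependence, all of which are collected at baseline. Motivation probably biases it upward, while targeting of dependent smokers could bias it downward. With no true effect, omitting motivation gives about 1.1 to 2.1 over the assumed range, with 1.38 in the middle. These figures show what is possible and do not estimate the bias in this cohort. A reader might infer that the study is bound to report a benefit of support that does not exist, but the documents do not support that.

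The timing point is secondary. It rests on the absence of any stated ordering together with shared visits, and its size (1.09 to 1.75) is equally assumption-driven.

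**What to change.** In the Statistical analysis section, name baseline motivation (0–10), quit attempts in the past year and Fagerström score as adjusters alongside substance and sex, and identify type of support as the exposure. Use baseline motivation, because Table 1 marks follow-up motivation only for participants who are not abstinent. Given the 16 to 20 expected abstinent participants, keep to this short list or enter it through one propensity score, and fix the choice before the data are analysed.

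Add an analysis, with the same adjusters, that relates abstinence at a visit to support recorded at an earlier visit. Describe the same-visit RR as an association, and list residual confounding among the limitations.

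The cost is analysis wording only, since every variable is already collected. Intervals will be somewhat wider, and support first recorded at the outcome visit will not be credited in the lagged analysis. Lagging orders the records but does not itself remove confounding, so it supplements the adjustment and does not replace it.

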(4) Identify and compare the level of implementation of smoking cessation services reported by patients and clinicians.

The purpose of this manuscript is to report the methodology employed in the ongoing ACT-ATAC project and the experience of carrying out and adjusting this study during the social restrictions put in place due to the COVID-19 pandemic.

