### Cohort of clinicians

#### Participants

Clinicians from the province of Barcelona who agree to participate in the study must meet the following inclusion criteria: (1) to be a clinician (psychologist, psychiatric, nurse, social worker, etc.) in one of the public SUD programs in the province of Barcelona, and (2) that does the initial assessment and follow-up of persons with alcohol and/or cannabis abuse disorders, and (3) provides consent. The exclusion criterion is an inability to guarantee a 12-month follow-up (due to anticipated moves, etc.). We expected to include between 20 and 30 clinicians, and 22 clinicians are currently collaborating in the study from 10 different SUD centers.

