#### Variables

The primary dependent variable is self-reported smoking knowledge, attitude, and practice (S-KAP) [48] during the clinician’s work in the SUD program, monitored at baseline of their participation, one week after, and every three months during their participation in the study.

Independent variables are tobacco consumption (never user, former user, and current user), sociodemographic data (sex, age, education level, profession), and professional experience (years treating drug abuse population, years working in the same program). In the case of being a tobacco user, we ask about the tobacco product consumed (i.e., cigarettes, roll-your-own tobacco, combination of both, cigars, e-cigarettes, iQOS); smoking history, including age when starting smoking, maximum abstinence time, previous quitting attempts, and resources used (i.e., none, self-help, professional support, pharmacological treatment, etc.); motivation to quit smoking, measured by a Likert scale from 0 to 10; and willingness to quit smoking, assessed by a 4-item questionnaire according to Prochaska and DiClemente’s model, classifying smokers into five stages of change [36].

Clinicians receive the KAP questionnaire [48] every three months to report data on the approach taken in the care of the smoker (ask, advise, assist).

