## Discussion

Over the course of the study, the COVID-19 pandemic forced us to adjust some parts of the study without changing its purpose or the core elements of its methodology. The most notable adjustment has been to replace face-to-face follow-up interviews with telephone-based interviews and to extend the study another year to ensure we recruit enough participants to have enough statistical power to conduct the analysis. All of the changes have been possible thanks to the successful collaboration between the coordinators, the clinicians, and the Public Agency of Public Health in Catalonia. The ACT-ATAC team has worked together in setting up multiple videocalls to keep the study on track.

In addition to the pandemic, another significant challenge faced by the ACT-ATAC research group was designing ad hoc baseline and follow-up questionnaires, particularly regarding the description of type of products and pattern of consumption for cannabis. Unlike the measurement for alcohol use, there are few validated questionnaires designed to monitor the consumption of cannabis (alone and in combination with tobacco). Therefore, we conducted a thorough review following recent recommendations [50–52] and developed a battery of questions to address the mode and frequency of consumption (i.e., marijuana, hashish, CBD oil) and its interaction with tobacco products in the past 30 days. The validity of these questions will be tested in the study and will be shared with the scientific community.

Moreover, we have included two scales used in the US to assess “Smoking-related Knowledge, Attitudes, and Services (KAS)” among users [42] and “Smoking-related Knowledge, Attitudes, and Practices (KAP)” [48] among providers. These scales were validated in the US, but their validity has not been assessed in Spanish. Therefore, we decided to translate them and validate their psychometric proprieties for the Spanish population. This work will allow us to have a valid Spanish language instrument to measure relevant variables in the tobacco control dimensions related to the views of users and staff. This validation is an added value for mental health professionals and decision-makers, as these scales could be of help in understanding how smoking cessation services are provided in SUD programs.

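### The S-KAP factor analysis rests on 20 to 30 clinicians and cannot be relied on as validation, and aim 4's patient-clinician comparison is assigned to a substudy with no clinicians

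*Protocol article*

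**What the plan says.** **Factor analysis.** The Statistical analysis section plans "exploratory factor analysis for testing the psychometric properties of the S-KAS and S-KAP scales". S-KAP is the clinicians' instrument (Cohort of clinicians, Variables). On the size of that cohort, the Participants section says: "We expected to include between 20 and 30 clinicians, and 22 clinicians are currently collaborating in the study from 10 different SUD centers". Each clinician's S-KAP is "monitored at baseline of their participation, one week after, and every three months". The Discussion notes that neither scale's validity has been assessed in Spanish, sets out to validate both, and concludes: "This work will allow us to have a valid Spanish language instrument", covering the views of users and staff.

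**Aim 4.** The Background states it as: "Identify and compare the level of implementation of smoking cessation services reported by patients and clinicians". The introduction to S2, under Procedures and statistical analysis, gives S2 aims 2 and 3. The S3 paragraph at the end of Statistical analysis says that the discussion-group study "will use a semi-structured script to answer aim 4". S3 participants are drawn from the S2 smoker cohort. Their topics are barriers to quitting, the approach to smoking they received, and their opinion of the service.

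**The concern.** Two separate points are raised because both concern what the S-KAP data are used for.

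First, a factor analysis works on the matrix of inter-item correlations. With about 22 respondents each correlation is very imprecise, so the factors extracted may reflect sampling error. A statistical analysis plan could add rules for retention or rotation, but it would not change the number of clinicians. If the output is published as validation, later users of the Spanish S-KAP would adopt subscales with little evidence behind them.

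Second, a comparison of two sources needs both sources. The substudy named for aim 4 has one, and the substudy that has both is not named for it. Followed literally, the plan attaches a stated aim to data that cannot deliver it alone.

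**Working it through.** The documents give no sample-size figure for the factor analysis or for aim 4, so there is no planned figure to reproduce.

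**Inputs from the article:** S-KAP respondents 20 to 30, currently 22; S-KAS respondents at least 200 to 250; S-KAP at baseline, one week and every three months. **Assumptions, because not given:** 12 to 32 items, 3 or 4 factors, loadings of 0.5 to 0.7, and six forms per clinician over 12 months (baseline, one week, months 3, 6, 9 and 12).

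**Step 1: precision of one inter-item correlation.** By Fisher's z, the 95% band for a true zero correlation is ± tanh(1.96/√(n − 3)).
- n = 22: tanh(1.96/√19) = tanh(0.450) = 0.42.
- n = 30: tanh(1.96/√27) = tanh(0.377) = 0.36.

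The interval for an observed r is tanh(atanh r ± 1.96/√(n − 3)):

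| Observed r | n = 22 | n = 200 |
|---|---|---|
| 0.3 | −0.14 to 0.64 | 0.17 to 0.42 |
| 0.5 | 0.10 to 0.76 | 0.39 to 0.60 |

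At n = 22 an observed correlation of 0.3 is compatible with no relation and with a strong one. If the scale has 22 or more items, the sample correlation matrix is also singular, since its rank is at most 21.

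**Step 2: recovery of a known structure.** Simple-structure data were simulated and analysed by principal-axis extraction with varimax rotation, 200 runs per setting. Recovery means a minimum congruence of at least 0.85 with the true factors. The number of factors was scored separately, by parallel analysis at the 95th percentile. Ranges are over the assumed item and factor counts.

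| Loadings | Recovery, n = 22 | Right number of factors, n = 22 | Recovery, n = 30 |
|---|---|---|---|
| 0.5 | 0 to 3% | 3 to 27% | 1 to 10% |
| 0.6 | 7 to 34% | 15 to 55% | 24 to 79% |
| 0.7 | 55 to 93% | 34 to 92% | 90 to 100% |

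At n = 200 to 250, the planned S-KAS size, recovery was 99 to 100% in every setting.

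**Step 3: do repeat forms help?** Six forms from 22 clinicians make 132 forms. With intraclass correlation ICC between forms of the same clinician, the effective number is 132/(1 + 5 × ICC):
- ICC 0.9: 132/5.5 = 24.
- ICC 0.3: 132/2.5 = 53.

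Pooling therefore adds little unless a clinician's answers are only weakly stable over time.

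**Step 4: aim 4, source by source.**

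| | Patient report | Clinician report | Aims assigned |
|---|---|---|---|
| S2 | S-KAS and cessation services received | S-KAP and the ask, advise, assist approach | 2 and 3 |
| S3 | Discussion groups | None | 4 |

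The recruitment software also records each patient's responsible clinician (Recruitment process and fieldwork), so the two reports in S2 appear linkable.

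**The case against.** **On the factor analysis.** The shortfall depends on item count, number of factors and loadings, none of which is given. With uniform loadings of 0.7, recovery reached 55 to 93% at n = 22 and 90 to 100% at n = 30, the top of the expected range. A reader might infer that a structure cannot be obtained at all, or that whatever emerges must be an artefact; the documents do not support that. What remains is that the loadings of the Spanish version are unknown beforehand, so an analysis that is dependable only if they are high cannot itself establish validity. A reader might also argue from the number of eigenvalues above 1 in pure noise. That does not help: with 20 items it averages about 8.1 at n = 22 and 9.4 at n = 200, so it shows no small-sample problem, and the article names no such rule.

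**On aim 4.** A reader might infer that aim 4 will go unanswered, or that no quantitative comparison is planned. Neither follows. S2 collects both sides, and the Abstract and the Limitations and strengths section announce triangulation of data sources. The article condenses a fuller protocol, which may hold the comparison method, so its absence here is no defect. This objection stands in full. It leaves the explicit assignment of aims to substudies, which a general statement about triangulation does not correct.

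**On importance.** Neither point touches the abstinence and quit-attempt analyses. That is correct and limits the weight of both.

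**Conclusion.** Both points hold in a limited form.

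1. An exploratory factor analysis of S-KAP on 20 to 30 clinicians is unreliable, and its result should not be presented as validation for staff. The ±0.42 band at n = 22 (±0.36 at n = 30) follows from the sample size alone. The recovery rates of 0 to 34% rest on assumed loadings of 0.5 to 0.6 and on assumed item and factor counts. The criticism does not extend to S-KAS.
2. Aim 4 is assigned to the wrong substudy. S3 contains no clinicians, so S3 alone cannot compare patient and clinician reports, while S2 holds both. This is an inconsistency between the aims, the S2 introduction and the S3 paragraph; it rests on the text and needs no numerical assumption.

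The changes should be made, but the primary analyses do not depend on them.

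**What to change.** **S-KAP.** Limit the exploratory factor analysis to S-KAS. For S-KAP, report item distributions, internal consistency, and agreement between the baseline and one-week forms already scheduled, all labelled preliminary and with confidence intervals. These will be wide too: by the formula in step 1, a baseline to one-week correlation of 0.8 in 22 clinicians has an interval of tanh(1.099 ± 0.450), about 0.57 to 0.91. Restrict the Discussion's validity statement to what each scale's sample can support. The cost is a more modest claim for S-KAP.

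**Aim 4.** Assign it to S2. Compare each clinician's S-KAP practice items with the S-KAS services reported by that clinician's own patients, using the recorded responsible clinician as the link, and keep S3 as supporting qualitative material. At the revised target this gives on average about 200/22 = 9 to 250/22 = 11 patients per clinician, so the analysis should allow for clustering by clinician. The cost is wording in the S2 and S3 descriptions and a small analysis; no new data collection is needed.
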